### Secondary outcomes

- Decreased viral load on nasopharyngeal swab (days 6, 9 and 14)
- Decreased viremia at day 6 and 9
- Increased antibody titre against SARS-CoV2 (days 30 and 60)
- Proportion of patients with negative of SARS-CoV2 nasopharyngeal swab (day 60)
- Length of hospital stay
- Mortality rate at day 28
- Total plasma related adverse event (Febrile reactions, TRALI, TACO, TTI) (day 60)
- Total non-plasma related adverse events (day 60)
- Severe adverse events (SAE) (day 60)

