## APPENDIX B

### ADVERSE/SEVERE ADVERSE EVENT: DEFINITIONS AND MANAGEMENT

**Adverse Events** An ‘adverse event’ is defined in Article 2 (m) of Directive 2001/20/EC as follows: ‘Any untoward medical occurrence in a patient or clinical trial subject administered a medicinal product and which does not necessarily have a causal relationship with this treatment’. An adverse event can therefore be any unfavorable and unintended sign (including an abnormal laboratory finding, for example), symptom or disease temporally associated with the use of a medicinal product, whether or not considered related to the medicinal product

An “adverse event” is any worsening in the general condition of a subject, or a subject participating in a clinical experiment to whom a pharmaceutical product is administered, regardless of its relationship with the given treatment. An AE may also be any unexpected adverse sign (which can include an abnormal laboratory result of clinical significance), and each symptom or pathology temporarily associated with the use of a pharmaceutical product, regardless of its relationship with the same product. AEs may be **expected** (consistent with the information leaflet provided with the product) or **unexpected** (inconsistent with the information available).

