#### Adverse events include:

- The exacerbation of a pre-existing pathology;
- An increase in the frequency or intensity of an episodic event or pre-existing condition;
- A condition occurring or diagnosed after the administration of the study drug, even if current before the start of the study;
- Persistent diseases/symptoms at the baseline visit that worsen after the start of the study.

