#### Adverse events do NOT include:

- Medical or surgical procedures (e.g. surgery, endoscopy, tooth extraction, transfusions), but the condition requiring the procedure is an adverse event
- Diseases or conditions present at the beginning of the study that have not worsened, but remained stable during the course of the study.

- Situations in which no unexpected adverse event has occurred (e.g. hospital admission for elective cosmetic surgery/social problems).
- An overdose of antiviral agents or concomitant drugs without onset of symptoms or associated signs.
- Laboratory abnormalities deemed by the investigator to be of no clinical significance.

Adverse events will be graded according with CTCAE v5.0. (Appendix B) Grade 1 and Grade 2 events are not considered adverse events, but details of these events must be documented in detail in the subject's study files.

Stable chronic conditions which are present prior to clinical trial entry and do not worsen are not considered adverse events and will be accounted for in the subject's medical history.

**Serious Adverse Events (SAE's).** A 'serious adverse event' is defined in Article 2(o) of Directive 2001/20/EC as follows: 'Any untoward medical occurrence or effect that at any dose results in death, is life-threatening, requires hospitalization or prolongation of existing hospitalizations, results in persistent or significant disability or incapacity, or is a congenital anomaly or birth defect'. These characteristics/consequences have to be considered at the time of the event. For example, regarding a life-threatening event, this refers to an event in which the subject was at risk of death at the time of the event; it does not refer to an event which hypothetically might have caused death if it were more severe. Some medical events may jeopardize the subject or may require an intervention to prevent one of the above characteristics/consequences. Such events (hereinafter referred to as 'important medical events') should also be considered as 'serious' in accordance with the definition. Medical and scientific judgement should be exercised in deciding whether an event is 'serious' in accordance with these criteria

A Serious Adverse Event is defined as an SAE meeting one of the following:

- Death during the period of protocol-defined surveillance
- Life Threatening Event (defined as a participant at immediate risk of death at the time of the event)

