- In-patient hospitalization or prolongation of existing hospitalization during the period of protocol-defined surveillance

- Results in congenital anomaly or birth defect
- Results in a persistent or significant disability/incapacity

Any other important medical event that may not result in one of the above outcomes, may be considered a serious adverse experience when, based upon appropriate medical judgment, the event may jeopardize the participant and may require medical or surgical intervention to prevent one of the outcomes listed above.

**AE/SAE relationship assignment.** For all collected AE's/SAE's, the clinician who examines and evaluates the subject will determine the adverse event's causality based on temporal relationship and his/her clinical judgment. The degree of certainty about causality will be graded using the categories below:

- **Definitely Related:** There is clear evidence to suggest a causal relationship, and other possible contributing factors can be ruled out. The clinical event, including an abnormal laboratory test result, occurs in a plausible time relationship to drug administration and cannot be explained by concurrent disease or other drugs or chemicals. The response to withdrawal of the drug (de-challenge) should be clinically plausible. The event must be pharmacologically or phenomenologically definitive, with use of a satisfactory rechallenge procedure if necessary.
- **Probably Related:** There is evidence to suggest a causal relationship, and the influence of other factors is unlikely. The clinical event, including an abnormal laboratory test result, occurs within a reasonable time sequence to administration of the drug, is unlikely to be attributed to concurrent disease or other drugs or chemicals, and follows a clinically reasonable response on withdrawal (de-challenge). Re-challenge information is not required to fulfill this definition.
- **Possibly Related:** There is some evidence to suggest a causal relationship (e.g., the event occurred within a reasonable time after administration of the trial medication). However, the influence of other factors may have contributed to the event (e.g., the subject's clinical condition, other concomitant events). Although an adverse drug event may rate only as "possibly related" soon after discovery, it can be flagged as requiring more information and later be upgraded to "probably related" or "definitely related", as appropriate.

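### COVID-19 worsening counts as an adverse event and usually as an SAE, so the SAE and non-plasma AE outcomes overlap heavily with the primary outcome and can hide other serious harm

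*Protocol*

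**What the plan says.** The phase III secondary outcomes list three adverse-event outcomes, all to day 60. The first is plasma-related events, naming febrile reactions, TRALI, TACO and TTI. The other two are "Total non-plasma related adverse events (day 60" and "Severe adverse events (SAE) (day 60".

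Appendix B supplies the definitions. (The sentence after the outcome list points to Appendix C, but the definitions stand in Appendix B.) An adverse event is "any worsening in the general condition of a subject, or a subject participating in a clinical experiment", whatever its relation to treatment. The list of what is included names "The exacerbation of a pre-existing pathology" and "Persistent diseases/symptoms at the baseline visit that worsen after the start of the study". The nearest exclusion is "Diseases or conditions present at the beginning of the study that have not worsened, but remained stable during the course of the study". A further limit says "Grade 1 and Grade 2 events are not considered adverse events". Nothing exempts progression of COVID-19 or events already counted in the primary outcome.

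The SAE criteria include death, a life-threatening event, and "In-patient hospitalization or prolongation of existing hospitalization during the period of protocol-defined surveillance".

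The primary outcome is the proportion of patients without a 2-point worsening on the Appendix C scale within day 14. The treating clinician grades causality (Appendix B), and the Blinding section leaves care providers, outcome assessors and analysts unmasked.

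**The concern.** Every enrolled patient has COVID-19 pneumonia at baseline, so its worsening falls inside the adverse-event definition. On the Appendix C scale, a 2-point worsening takes a patient from level 5 to non-invasive ventilation or high-flow oxygen, or from level 4 to invasive ventilation or ECMO; a larger fall can end in death. These events will usually meet an SAE criterion. The SAE outcome and the non-plasma AE outcome therefore carry much of the efficacy signal.

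The only adverse-event outcome that leaves COVID-19 worsening out is the plasma-related one. It rests on unblinded attribution and has no counterpart in a control arm that receives no plasma. The stopping rule has the same limits: it counts only arm A events judged connected with the infusion.

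What is at stake is a between-arm excess of serious events that are not recognised as plasma-related. If plasma prevents progression, the fall in COVID-19 SAEs can offset that excess. If plasma does nothing for progression, the common COVID-19 events dilute it. The Trial design section itself says that data on patients at this earlier phase of disease are lacking.

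**Working it through.** **Inputs from the protocol.** Progression 40% in control and 20% with plasma; 91 per arm; two-sided 0.05 (Sample size, phase III). Chi-square or Fisher's exact test for categorical secondary endpoints (Statistical methods).

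**The plan's own figure.** The two-proportion formula with continuity correction for 40% vs 20%, two-sided 0.05 and 80% power gives 91 per arm, as stated. Exact Fisher power at 91 per arm is 80.8%. The protocol gives no figure for the SAE outcome.

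**Assumed, not in the protocol.** Other SAEs occur in 5% of controls, independently of progression. A share *q* of progressions meets an SAE criterion, with *q* = 100%, 75% or 50%.

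**Formula.** P(any SAE) = 1 − (1 − progression × *q*) × (1 − other-SAE rate).

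**Other SAEs tripled by plasma (5% vs 15%).**
- *q* = 100%: control 1 − 0.60 × 0.95 = 43%; plasma 1 − 0.80 × 0.85 = 32%.
- *q* = 75%: control 1 − 0.70 × 0.95 = 33.5%; plasma 1 − 0.85 × 0.85 = 27.8%.
- *q* = 50%: control 1 − 0.80 × 0.95 = 24%; plasma 1 − 0.90 × 0.85 = 23.5%.

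Exact Fisher, 91 per arm, two-sided 0.05:

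| Share of progressions that are SAEs | Any SAE, control vs plasma | Significant in favour of plasma | Significant excess with plasma |
|---|---|---|---|
| 100% | 43% vs 32% | 28.9% | 0.01% |
| 75% | 33.5% vs 27.8% | 10.2% | 0.2% |
| 50% | 24% vs 23.5% | 2.0% | 1.4% |

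**Break-even.** The other-SAE rate with plasma at which the two totals are equal is 1 − 0.95 × (1 − 0.40*q*)/(1 − 0.20*q*). This gives 28.75%, 21.8% and 15.6% for *q* = 100%, 75% and 50%, against 5% in control.

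**Plasma without effect on progression.** With 40% progression in both arms and *q* = 100%, the totals are 43% vs 1 − 0.60 × 0.85 = 49%. The excess is flagged with about 9% probability. This is dilution, not reversal.

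**Other SAEs counted on their own.** 5% vs 15% is detected with 53.3% probability, and 5% vs 10% with 16.8%.

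**Where the masking ends.** With other SAEs at 10% in control and *q* = 50%, a doubling to 20% is exactly hidden (28% vs 28%). A tripling to 30% shows as 37% vs 28% and is flagged with 20.8% probability.

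**The case against.** A reader might infer that the SAE outcome does not measure safety at all, or that it will probably make plasma look safer. The documents support neither. All-cause SAEs measure net serious harm: if plasma removes 20 points of progression and adds 10 points of other events, fewer patients do suffer an SAE. That is a real result and a reason to keep the outcome. The apparent benefit also depends on nearly every progression being an SAE. Level 3 of the scale includes high-flow oxygen, which need not always qualify, and at a 50% share the apparent benefit almost vanishes. What remains across the three shares is the low chance of seeing the excess.

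The overlap is large but not complete: SAEs run to day 60 and the primary outcome to day 14. The outcome list says severe where Appendix B defines serious, though progression to ventilatory support would usually count under either word.

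The tripling has no source in the protocol. The Benefit/risk section puts allergic or febrile reactions and TACO at about 1 in 100 each. A 10-point excess in 91 patients is about 9 patients, which would pass the six-patient stopping rule if the events were recognised as plasma-connected. The point therefore concerns harm that goes largely unattributed. That is possible, because TRALI and TACO are respiratory and attribution is unblinded, but it is narrower than all harm from plasma.

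It can also be said that splitting SAE tables belongs in the statistical analysis plan, which is not at hand. That is fair for table layout. The adverse-event definitions and the outcome list, however, are fixed in the protocol, and the overlap follows from those two together.

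**Conclusion.** The concern holds as a heavy overlap with the primary outcome. The listed between-arm SAE and non-plasma AE outcomes cannot separate fewer COVID-19 events from more events of other kinds. In the 5% vs 15% illustration the SAE total flags the excess with at most 1.4% probability whichever share is assumed, against 53% for a separate count. The chance of a significant result in favour of plasma ranges from 29% down to 2% with the share.

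These figures rest on assumed other-SAE rates, independence from progression, and the planned effect on progression. The phase II sample-size text words the rates the other way round (20% to 40% without progression); the phase III wording is used here. The overlap itself follows from the definitions and needs none of these assumptions. All-cause SAEs stay valid as a net measure, and recognised transfusion reactions stay visible in their own outcome. This should be corrected, but it does not undermine the trial.

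**What to change.** Leave the all-cause SAE outcome and its collection unchanged. Add to the phase III secondary outcomes one prespecified by-arm comparison, over the same 60 days: patients with any SAE other than COVID-19 respiratory worsening or COVID-19 death.

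Define the excluded events by the Appendix C scale, as a respiratory move to a worse level or a COVID-19 death at any time to day 60. Do not reuse the primary-outcome definition: it would leave in the count any 1-point worsening that prolongs the stay and any progression after day 14. Keep every event diagnosed as a transfusion reaction in the new count, even if it also moves the patient down the scale.

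The cost is one definition and one table from data already collected. The downsides should be stated beside it:
- It is supportive, with limited power (17% for 5% vs 10%).
- It may miss disease enhancement, or unrecognised TRALI or TACO, that looks like progression.
- Complications of progression, and early deaths that preclude later events, can still carry some efficacy signal.
- Classification is unblinded.

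For these reasons it is read together with the all-cause count and never replaces it.

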Appendix C provides the definitions for adverse events and severe adverse events.

## Timeline

The study timeline is shown in the Gantt diagram (Appendix D)

## METHODS: STUDY ASSESSMENT AND PROCEDURES

### Procedures and visits

A study flow-chart is shown in Appendix E.

#### Screening phase: day -1

#### Baseline visit: day 0:

Physical examination and vital signs (blood pressure, heart rate, respiratory rate, temperature), Respiratory status (pO2/FiO2 and SpO2 at rest if applicable), ECG; blood sampling for ABO groups (on two separate samples), RT-PCR for SARS-CoV-2 on nasopharyngeal swab. routine blood tests (blood count, creatinine, BUN, sodium, potassium, ALT, AST, LDH, fibrinogen, D-dimer, ferritin, CRP), viremia, anti SARS-Cov-2 antibody screening, IL6.

**Plasma administration: days 1,2, 3.** All patients will sign the informed consent to receive blood products in use at each center.

**Daily study assessment: days 1 to 14**

Physical examination and vital signs (blood pressure, heart rate, respiratory rate, temperature, oxygen supplementation), Respiratory status (pO2/FiO2 and SpO2 at rest if applicable), ECG and chest scan (on day 7 and 14, or additional days if clinically advised); routine blood tests (blood count, creatinine, BUN, sodium, potassium, ALT, AST, LDH, fibrinogen, D-dimers, ferritin, CRP, every three days unless clinically advised), RT-PCR SARS-Cov2 on rhino-pharyngeal swab at the same time points of routine blood tests until 2 consecutive negative swabs within 24 hours, viremia (day 6, day 9, day 12 and day 14), anti SARS-Cov-2 antibody screening (day 14), IL6 (day 3, day 6, day 9).

**Day 15 visit (or visit at discharge)**

Physical examination and vital signs (blood pressure, heart rate, respiratory rate, temperature)

**Day 30 visit**

physical examination and vital signs and data on respiratory status and oxygen supplementation, anti SARS-Cov-2 antibody screening

**Day 60 visit**

physical examination and vital signs and data on respiratory status and oxygen supplementation, anti SARS-Cov-2 antibody screening.

**Sample size**

**Phase II.** To demonstrate that adding CCP to standard therapy is associated with an increase of proportion of patients without progression from 20% (control, Arm B) to 40% (treatment, Arm A), with a 80% power and a two-tailed alpha error of 0.2, 114 (57 per arm) evaluable patients are needed, with an OR for treatment of 0.375.

**Phase III.** To demonstrate that adding CCP to standard therapy is associated with a reduction of the proportion of patients progressing to severe pneumonia from 40% (control, Arm B) to 20% (treatment, Arm A), with a 80% power and a two-tailed alpha error of 0.05, 182 (91 per arm) evaluable patients are needed, with an OR for treatment of 0.375.

Chow, SC, Shao J and Wang H. 2003. Sample Size Calculations in Clinical Research. Marcel Dekker. New York.

**Recruitment**

Patients are recruited at three different COVID centers (Fondazione Policlinico Gemelli IRCCS, Istituto Nazionale Malattie Infettive Lazzaro Spallanzani and Policlinico SS Annunziata Chieti). Convalescent plasma

will be collected at Fondazione Policlinico Gemelli IRCCS, Azienda Ospedaliera San Camillo Forlanini and Ospedale SS Annunziata Chieti.

## **METHODS: ASSIGNMENT OF INTERVENTIONS**

### **Allocation and sequence generation**

Treatment allocation will be randomized between arms A and B with a ratio 1:1 and will be the same in phase II and phase III. Randomization sequences will be generated at Fondazione Policlinico Gemelli IRCCS.R through the RedCap web application, uploading the allocation table through the randomization module (ref: <https://www.project-redcap.org/>).

Randomized stratification will be performed according to age (under/over 80 years), and sex.

**Blinding (masking)** The assignment to intervention will be unmasked to all trial participants (care providers, outcome assessors, and data analysts)

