## OUTCOMES AND ENDPOINTS

|                 |                                                                                                                                                                                                                                                                                                                                                                                                                                                                                    |
|-----------------|------------------------------------------------------------------------------------------------------------------------------------------------------------------------------------------------------------------------------------------------------------------------------------------------------------------------------------------------------------------------------------------------------------------------------------------------------------------------------------|
| Phase II | 
Primary outcome
 
 
– Proportion of patients without progression in severity of pulmonary disease defined as worsening of 2 points in the ordinal scale of WHO within day 14.
 
 
The WHO ordinal scale to assess the disease progression is provided in Appendix C.
 
Secondary outcome
 
 
– Decreased viral load on nasopharyngeal swab (days 6 and 9)
 
 |
|-----------------|------------------------------------------------------------------------------------------------------------------------------------------------------------------------------------------------------------------------------------------------------------------------------------------------------------------------------------------------------------------------------------------------------------------------------------------------------------------------------------|

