## APPENDIX C

### WHO ORDINAL SCALE FOR ASSESSING PROGRESSION OF PNEUMONIA

1 = Death;

2 = Hospitalized, on invasive mechanical ventilation or extracorporeal membrane oxygenation (ECMO);

3 = Hospitalized, on non-invasive ventilation or high flow oxygen devices;

4 = Hospitalized, requiring supplemental oxygen;

5 = Hospitalized, not requiring supplemental oxygen;

6 = Not hospitalized

1. Coronavirus disease (Covid-19) R&D. Geneva: World Health Organization

<https://www.who.int/blueprint/priority-diseases/key-action/novel-coronavirus/en/>

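### Outcome assessors and data analysts are unmasked without need, and the non-fatal part of the primary endpoint rests on device decisions by staff who know the allocation, with no physiological check

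*Protocol*

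**What the plan says.** The blinding statement under Methods: Assignment of Interventions leaves the allocation "unmasked to all trial participants (care providers, outcome assessors, and data analysts". No reason is given for including assessors and analysts.

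Under Outcomes and Endpoints, progression is "defined as worsening of 2 points in the ordinal scale of WHO within day 14", in the same words for Phase II and Phase III. In Appendix C a lower number is worse, and death is category 1. Category 5 is "Hospitalized, not requiring supplemental oxygen", category 3 is "Hospitalized, on non-invasive ventilation or high flow oxygen devices", and category 2 is "Hospitalized, on invasive mechanical ventilation or extracorporeal membrane oxygenation (ECMO".

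The section headed "Daily study assessment: days 1 to 14" schedules vital signs including respiratory rate, oxygen supplementation, and PaO2/FiO2 and SpO2 at rest. The last two are to be taken only if applicable. The Rationale gives a physiological description of severe disease (dyspnea, respiratory rate, saturation, PaO2/FiO2, growth of infiltrates). The stated objective and the Phase III sample size text both speak of progression to severe pneumonia.

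The protocol states no criteria for starting a device and no masked or central adjudication. The monitoring section describes source verification.

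**The concern.** Two features combine. First, a non-fatal event is recorded when somebody starts a device, and that person knows the arm. If the threshold for starting differs between arms, recorded progression differs even when the disease does not, and a larger sample does not remove the difference. Second, the people who turn the chart into a category and then into a result also know the arm, although nothing in the treatment comparison requires it.

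The stakes are concentrated in one place. This endpoint decides whether Phase III starts, at a two-sided alpha of 0.2, and it also carries the Phase III claim. Source verification can confirm that a device was used. It cannot show that the threshold for using it was the same in both arms.

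**Working it through.** **1. What makes a non-fatal event.** Reading the definition as a worsening of at least 2 points:
- from category 5 (the expected entry state, since mild pneumonia is described as needing no oxygen), the patient must reach category 3: non-invasive ventilation or high-flow oxygen;
- from category 4, the patient must reach category 2: invasive ventilation or ECMO;
- death is at least 2 points from any category except 2.

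Oxygen supplementation does enter the scale, because it separates category 4 from category 5. PaO2/FiO2, SpO2 and respiratory rate do not.

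**2. The plan's own figures.** Inputs from the Sample size section: 40% against 20%, 80% power, two-sided alpha 0.2 (57 per arm) and 0.05 (91 per arm).

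n = [z(1−α/2)·√(2·0.3·0.7) + z(0.8)·√(0.4·0.6 + 0.2·0.8)]² / 0.2², then the continuity correction n′ = (n/4)·[1 + √(1 + 4/(0.2n))]².
- Alpha 0.2: (1.2816·0.6481 + 0.8416·0.6325)²/0.04 = 46.4, and n′ = 56 (stated 57).
- Alpha 0.05: (1.9600·0.6481 + 0.8416·0.6325)²/0.04 = 81.2, and n′ = 91 (stated 91).

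Exact Fisher power at the stated sizes is 80.7% and 80.8%. The design figures therefore reproduce.

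**3. Effect of an ascertainment shift.** The Statistical methods section specifies Fisher's exact test. With i progressions in control and j in arm A:

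P(favours plasma) = Σᵢ Σⱼ Bin(i; n, π_B)·Bin(j; n, π_A)·1[i > j]·1[two-sided Fisher p ≤ α].

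Assumptions: no true effect, π_B = 40%, and recorded π_A lowered by the shift. The documents give no shift size, so a range is shown.

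| Shift in arm A | Patients (of 57; of 91) | Phase II | Phase III alone |
|---|---|---|---|
| 0 | 0; 0 | 7.6% | 1.8% |
| 3 points | 1.7; 2.7 | 13.2% | 4.7% |
| 5 points | 2.9; 4.5 | 18.4% | 8.2% |
| 8 points | 4.6; 7.3 | 28.4% | 16.6% |
| 10 points | 5.7; 9.1 | 36.4% | 24.7% |

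For scale, with 23/57 control progressions significance needs 15/57 or fewer in arm A. With 36/91 it needs 22/91 or fewer.

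**4. Base rate.** The Phase II text puts non-progression in control at 20%, which is 80% progression. On that reading a 5-point shift moves the figures from 6.8% to 19.9% and from 1.6% to 9.3%. At 20% progression in both arms it moves them from 6.8% to 21.1% and from 1.6% to 10.4%. The pattern does not depend on which rate is meant.

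**5. The gate.** Phase III starts only if Phase II succeeds. The protocol does not say whether the Phase II patients count within the 91 per arm. With a 5-point shift, the chance of passing both stages is 0.184 × 0.082 = 1.5% if Phase III enrols new patients. It is about 6.5% if the 57 per arm are part of the 91 (same enumeration, with 34 added per arm). With no shift these are 0.1% and 1.4%.

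**6. The opposite direction.** If plasma truly lowers progression from 40% to 20% but recorded arm A progression is 5 points too high (25%), the same formula gives 59.2% in Phase II and 52.4% in Phase III, against 80.7% and 80.8%.

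**The case against.** The other side has real strength.
- **Direction.** A reader might infer that open-label care biases the result towards plasma. The documents do not support that. The benefit/risk section lists circulatory overload, acute lung injury and antibody-dependent enhancement as risks of plasma, so staff could equally watch arm A more closely and escalate sooner. This stands.
- **Size.** No shift is documented. At 5 points, about 82% of Phase II and 92% of Phase III comparisons would still show no significant benefit. This stands: a small shift inflates the error rate but does not usually produce a positive trial on its own.
- **Mechanism.** The device in use is a recordable fact, and Fisher's test leaves the analyst little latitude. The larger exposure is the bedside decision, which masking the assessor or analyst does not touch. This stands and limits what the fix can achieve.
- **Timing.** A one-day delay in escalation rarely alters a binary day-14 outcome. This stands: what matters is whether escalation happens at all by day 14.
- **Physiology.** A reader might infer that none of the daily respiratory data enters the endpoint, or that a complete daily series exists. Neither is right. Oxygen supplementation enters the scale, and PaO2/FiO2 and SpO2 are conditional.
- **Death.** It counts as progression and is not open to this bias. Its share of events is not given.
- **A SAP may cover derivations and supportive analyses.** That is possible, and their absence from the protocol is not the fault raised here. The unmasking of assessors and analysts, however, is fixed in the protocol itself.

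**Conclusion.** The point holds in a limited form. The protocol unmasks outcome assessors and data analysts when the comparison does not require it. The non-fatal part of its only primary endpoint depends on support decisions by staff who know the allocation, and the scheduled respiratory measurements are not used as a check.

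Neither the direction nor the size of any bias can be derived from the documents. The 5-point illustration (7.6% to 18.4% in Phase II; 1.8% to 8.2% in Phase III taken alone, against a nominal 2.5% in that direction) assumes no true effect, 40% progression and a shift favouring plasma. The Phase III figure is before the Phase II gate. A shift the other way would instead cost power. The trial remains usable. This is an avoidable weakness that should be reduced, not evidence that the result will be wrong.

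**What to change.** 1. Amend the blinding statement so that the analyst works on coded arm labels, with plasma-infusion fields held back, until the endpoint derivation is locked. Unmasked care providers can remain.
2. Derive the Appendix C category by program from the daily eCRF fields for device, oxygen, hospitalisation and vital status, not from an unmasked assessor's score.
3. Report PaO2/FiO2, SpO2 and respiratory rate at escalation by arm. Add a supportive analysis in which progression is death, or a physiological criterion for severe disease already stated in the Rationale and met by day 14, whether or not a device was started. The investigators should name in advance which of those criteria count.

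Counting the criterion regardless of device matters. Requiring both a device and an abnormal value could remove patients escalated too readily, but could never recover those escalated too late or not at all.

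The cost is protocol wording, a coded REDCap export and some programming, with no extra staff or measurements. The downside is missing values where no blood gas was taken. The remedy is partial: it makes unequal escalation visible and removes the avoidable unmasking, but the bedside decision stays open.
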